# Multi-center, randomized, double-blind, placebo-controlled, exploratory study to evaluate the efficacy and safety of HAD-B1 for dose-finding in EGFR positive and locally advanced or metastatic NSCLC subjects who need Afatinib therapy

**DOI:** 10.1097/MD.0000000000018735

**Published:** 2020-01-24

**Keywords:** afatinib, HAD-B1, herbal medicine, non-small cell lung cancer, randomized controlled trial

## Abstract

**Background::**

In recent studies, afatinib, a second-generation inhibitor, showed superior outcomes, when compared to the first-generation of EGFR-tyrosine kinase inhibitors (TKIs), such as erlotinib and gefitinib, in patients with advanced non-small cell lung cancer (NSCLC) harboring mutations of epidermal growth factor receptor (EGFR). Patients who receive TKIs with a significant initial efficacy, inevitably experience an acquired resistance (AR) within 9 to 13 months. Traditional Korean medicine may have synergistic effects when combined with chemotherapy or radiotherapy. The purpose of this trial is to assess whether afatinib plus HAD-B1 improves disease control rates (DCRs) compared with afatinib alone and to evaluate the efficacy and safety of HAD-B1 for finding the proper dose.

**Methods::**

This is a randomized, double-blind, placebo-controlled, multi-center, therapeutic, exploratory clinical trial. This trial is designed to determine whether HAD-B1 combined with afatinib results in better DCRs with less toxicity than afatinib alone. A total of 66 NSCLC patients with EGFR mutations will be randomly assigned to treatment group 1 (afatinib 40 mg/day plus HAD-B1 972 mg), treatment group 2 (afatinib 40 mg/day plus HAD-B1 1944 mg) and a control group (afatinib 40 mg/day). Afatinib combined with HAD-B1 or with a placebo will be administered to the participants for 12 weeks. The primary endpoint is a comparison of the DCRs among groups. Secondary endpoints are comparisons of the complete response (CR) and the partial response (PR) to the treatment, the stability of the disease (SD), progression free survival (PFS), time to progression (TTP), and tumor marker (CEA, NSE) and WBC differential count (LMR, NLR) and natural killer cell activity and quality of life (QOL) among groups.

**Discussion::**

The results from this clinical trial will provide evidence of efficacy and safety of HAD-B1 in EGFR positive and locally advanced or metastatic NSCLC patients who need afatinib therapy.

## Introduction

1

Lung cancer is one of the most common malignant tumors in the world and is the leading cause of cancer-related mortality in males and females, according to statistics gathered in the United States in 2017.^[1]^ Lung cancer is divided into small cell and non-small cell lung cancer (NSCLC). NSCLC accounts for more than 85% of all lung cancer cases.^[2]^ Even with several advances in the staging, diagnostic procedures and therapeutic options, the overall prognosis has little changed for the majority of patients with the overall 5-year survival having only slightly increased over the last decade from 15.7% to 17.4%.^[3]^

Since the 2000s, the understanding of the pathogenesis of lung cancer has broadened, and now NSCLC can be classified into several subtypes according to mutations such as those involving epidermal growth factor receptor (EGFR), anaplastic lymphoma kinase (ALK), ROS proto-oncogene 1 receptor tyrosine kinase (ROS1) and programmed cell death protein 1 (PD-1). In addition, the treatment of lung cancer using these mutations has changed remarkably.^[4]^ In particular, EGFR tyrosine kinase inhibitors (TKIs), such as gefitinib and erlotinib, have been reported in a randomized-controlled phase-3 trial to prolong the progression-free survival (PFS) and to improve the quality of life (QOL) when compared to conventional platinum-based chemotherapy.^[5,6]^

Afatinib is a second-generation target anticancer drug that blocks all three ErbB family members: EGFR (ErbB1), HER2 (ErbB2), and ErbB4. It is also more advanced than the first-generation target therapeutics, gefitinib and erlotinib, which block only EGFR. Afatinib has been reported to improve overall survival significantly in comparison to conventional standard therapy.^[7]^ However, despite these improved therapeutic results, patients undergoing EGFR-TKI maintenance therapy usually experience disease progression due to secondary resistance that develops after about 9 to 13 months. For this reason, if the cure rate is to be improved, studies to find ways to overcome, or at least alleviate, the resistance to anticancer drugs that may occur over time in patients undergoing EGFR-TKI maintenance therapy are crucial.^[4]^

In patients with NSCLC, chemotherapy (CT) combined with herbal medicine therapy can reduce CT toxicity, prolong survival rate, enhance immediate tumor response, and improve the score on the Karnofsky performance status scale (KPS).^[8]^ Also, herbal medicine can be considered an efficient and safe maintenance therapy strategy for patients who show no progression after first-line chemotherapy, including those with poor QOL.^[9]^ Moreover, traditional Korean medicine, when combined with conventional cancer treatment, may improve the survival rate due to a synergism among improved QOL, enhanced immunity and reduced side effects.

HAD-B1 (Table 1) is a medical substance in traditional Korean medicine. It is composed of *Panax ginseng C.A.*, *Panax notoginseng Radix*, *Cordyceps militaris*, and *Boswellia carterii BIRDWOOD* and has been reported to have an anti-lung-cancer effect in xenograft animal model experiments using A549 lung cancer cells and A549/CR cells.^[10,11]^ Therefore, in this study, we aim to assess whether or not afatinib plus HAD-B1 can improve the DCR compared with afatinib alone and to evaluate the efficacy and safety of HAD-B1 for finding the proper dose for patients with EGFR positive and locally advanced or metastatic NSCLC.

**Table 1 T1:**

Components of HAD-B1.

## Methods

2

### Trial design

2.1

This study is a randomized, double-blinded, placebo-controlled trial that aims to examine the efficacy and safety of HAD-B1 for EGFR positive and locally advanced or metastatic NSCLC patients who need afatinib therapy. Also, the results will provide the proper dosage of HAD-B1 for the patients. Participants will be randomized using a ratio of 1:1:1 into treatment group 1 (afatinib 40 mg/day plus HAD-B1 2 tablets (972 mg/day) plus placebo 2 tablets, treatment group 2 (afatinib 40 mg/day plus HAD-B1 4 tablets [1944 mg]) and control group (afatinib 40 mg/day plus placebo 4 tablets). Afatinib combined with HAD-B1 or placebo will be administered to the participants for 12 weeks (Table 2).

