### Outcome measures

2.6

The primary outcome is a comparison of the disease control rates (DCR) among treatment groups 1 and 2 and the control group after 12 weeks compared to baseline, which will be assessed from the date of randomization to 12 weeks, as determined by chest X-ray, CT or MRI according to the RECIST criteria.^[11]^

The secondary outcomes are comparisons of the complete response (CR) and the partial response (PR) to the treatment, the stability of the disease (SD), progression free survival (PFS), time to progression (TTP), and tumor marker (CEA, NSE) and WBC differential count (LMR, NLR) and natural killer cell activity and QOL (EORTC QLQ-C30) among treatment groups 1 and 2 and the control group after 6 weeks and 12 weeks compared to baseline.

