### Sample size calculation

2.9

The sample size was determined by considering the number of participants available, the minimum range of the efficacy assessment, and the expected dropout rate during the study period. When the first two factors were considered, the total number of participants required for each group was calculated as 15, for a total of 45. When a dropout rate of 30% was used for each group, the required number of participants was calculated as 22 (15/(1 – 0.3) = 21.43 ≒ 22). Thus, when all factors are considered, the number of participants to be registered for each group is 22, so a total of 66 patients will be recruited.

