### Analysis of first outcome variables

2.13

Descriptive statistics (number in each group, average, standard deviation, minimum value and maximum value) will be used for each variable affecting the DCR (CR, PR, and SD), and the results for the two test groups and the control at the last visit versus the results at baseline will be presented. The statistical significance of any difference found between test groups and the placebo group will be analyzed using chi squared test. If any difference among three groups (2 test groups and 1 placebo group) is found, Bonferroni or Duncan method will be used. Chi squared test between placebo group and treatment group 1, placebo group and treatment group 2 will be additionally conducted.

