### Safety assessment

2.15

Adverse reactions, symptoms and vital signs, and the results of routine physical examinations and complete blood analyses will be recorded at baseline prior to administration of the drug, at intermediate visits and at the final visit. Adverse events will be assessed throughout this clinical trial.

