## Discussion

3

Afatinib is an available drug that is administered orally. It is an ErbB family blocker that, in comparison with the first-generation EGFR-TKIs, irreversibly and selectively blocks signaling from all homodimers and heterodimers formed by EGFR and by the erb-b2 receptor tyrosine kinase 2 (HER2/ERBB2), HER3/ERBB3, and HER4/ERBB4 receptors.^[13,14]^ Recently, three studies on the role of afatinib have been published: a combined analysis of LuxLung 3 and 6^[15]^ and analyses of LuxLung 7^[16]^ and LuxLung8.^[17]^ In LuxLung 3 and 6, afatinib showed superiority over the first-generation EGFR-TKIs: only afatinib among EGFR-TKIs improved the overall survival in comparison with the platinum-based chemo doublet. In LuxLung 7, afatinib was compared with gefitinib in a phase 2 B, open-label, randomized, controlled trial of EGFR mutation-positive NSCLC in treatment-naive patients and showed significant improvement in progression-free survival (PFS) and time-to-treatment failure. In LuxLung 8, afatinib was compared with erlotinib in a phase 3, open-label, randomized, controlled trial involving patients with a stage IIIB or IV squamous cell carcinoma who had progressed after at least four cycles of platinum-based chemotherapy and who had shown significant improvements in PFS and OS. Despite remarkable outcome results, patients receiving EGFR-TKIs usually developed secondary resistance after approximately 9 to 13 months (median PFS: 9–12 months) and showed major adverse events grade 3 or higher, including diarrhea, rash or acne, and stomatitis or mucositis.^[16–18]^

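### The protocol promises the proper HAD-B1 dosage, but it tests 972 mg against 1944 mg only if the three-group test shows a difference, and the arms are too small to tell the doses apart

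*Protocol article*

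**What the plan says.** Dose-finding is in the title of the protocol article and in its stated aims. Section 2.1, Trial design, puts it as a definite outcome: "Also, the results will provide the proper dosage of HAD-B1 for the patients". Patients are allocated 1:1:1 to 972 mg, 1944 mg or placebo, all on afatinib. The primary outcome (section 2.6) is a "comparison of the disease control rates (DCR) among treatment groups 1 and 2 and the control group after 12 weeks compared to baseline".

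Section 2.13, Analysis of first outcome variables, fixes four things:

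- descriptive results for both test groups and the control;
- a chi-squared test of the test groups against placebo;
- a Bonferroni or Duncan step if the three groups are found to differ;
- two further tests, for which no condition is given: "Chi squared test between placebo group and treatment group 1, placebo group and treatment group 2 will be additionally conducted".

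Section 2.14 repeats this scheme for the secondary outcomes. On size, section 2.9 says "the total number of participants required for each group was calculated as 15, for a total of 45", raised to 22 per group for 30% dropout.

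The abstract also asks "whether HAD-B1 combined with afatinib results in better DCRs with less toxicity than afatinib alone". On safety, section 2.7 says that reported adverse events will be analysed, section 2.11 assigns a safety-group analysis, and section 2.15 says "Adverse events will be assessed throughout this clinical trial". No section says how the dose will be chosen.

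**The concern.** A trial that says its results will yield the right dose needs a planned way of comparing the doses. Here the pairwise tests that always run leave out the one contrast that bears on dose. That contrast depends on an overall test which, at this sample size, will often be non-significant even when HAD-B1 works.

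When the overall test is non-significant, the only pairwise inference left is two separate comparisons with placebo. One dose reaching significance and the other not does not show that the doses differ. A reader of the results could still take it that way and carry the wrong dose, or an unsupported preference, into the next trial.

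**Working it through.** **Sample size.** 15/(1 − 0.30) = 21.43, rounded up to 22; 3 × 22 = 66. The article's figure reproduces. The 15 per group has no stated alpha, power or DCR behind it, so it says nothing about the precision of a dose comparison. I use n = 15 (evaluable) and n = 22 (registered) as the two ends of the range.

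**Assumptions.** Two-sided alpha 0.05 and the DCRs below; the article gives neither.

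**Method.** Exact enumeration of three independent binomial counts.

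- Overall test: X² = Σ(xᵢ − n·p̄)² / [n·p̄(1 − p̄)], with p̄ = total/(3n), on 2 degrees of freedom.
- Pairwise test: X² = (a − b)² / [2n·q(1 − q)], with q = (a + b)/(2n), on 1 degree of freedom, uncorrected.
- Post-hoc dose comparison: the pairwise test at 0.05/3, run only if the overall test is significant.

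**Step 1: how often the post-hoc step is reached.**

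| DCR placebo/972/1944 | n | Overall test significant | Step not reached | Dose difference significant after the gate |
|---|---|---|---|---|
| 70/80/90% | 15 | 19% | 81% | 3% |
| 70/80/90% | 22 | 28% | 72% | 4% |
| 82/95/95% | 15 | 18% | 82% | (doses equal) |
| 82/95/95% | 22 | 28% | 72% | (doses equal) |
| 60/75/90% | 15 | 38% | 62% | 8% |
| 60/75/90% | 22 | 53% | 47% | 11% |
| 50/70/90% | 15 | 60% | 40% | 15% |
| 50/70/90% | 22 | 77% | 23% | 21% |

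Larger assumed effects open the gate more often. Even then, a true 20-point difference between the doses (70% versus 90%) is declared in only 15 to 21% of trials.

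**Step 2: would an unconditional test solve it?** For a true 85% versus 95%, exact power of the chi-squared test is 8.9% (n = 15) and 17.8% (n = 22). The 95% half-width is 1.96 × √[(0.85 × 0.15 + 0.95 × 0.05)/n] = 1.96 × √(0.175/n). That gives 21.2 points at n = 15 and 17.5 points at n = 22. By the usual formula, 80% power for 80% versus 90% needs 199 per arm, and for 75% versus 95% it needs 49 per arm.

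**Step 3: what the two placebo tests show when the doses are equal.** Take 95% for both doses and 82% for placebo.

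| Result against placebo | n = 15 | n = 22 |
|---|---|---|
| Neither dose significant | 79% | 61% |
| Both significant | 8% | 15% |
| Exactly one significant | 12.8% | 24.1% |
| – of which the overall test is also significant | 4.2% | 11.0% |
| – of which no post-hoc dose comparison runs | about 9% | about 13% |

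The last row is the difference: 12.8 − 4.2 = 8.6 and 24.1 − 11.0 = 13.1.

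**The case against.** The strongest reply is that the trial calls itself exploratory, that the primary endpoint compares all three groups, and that results are shown for each arm. A descriptive dose comparison is therefore available whatever the tests show. Placing post-hoc contrasts behind an overall test is conventional. All of this stands, and it would be wrong to say that the doses are never compared.

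It is also fair to say that an extra significance test would add little. The main limit is 15 to 22 patients per arm. That argues for estimation in place of another test. It does not rescue a definite statement that the results will provide the dose.

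Four stronger readings are tempting, and the document does not support them:

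- **The dose will be picked by which arm is significant against placebo.** No section states a selection rule. This is an inference about how results might be read.
- **The risk is the full 13% or 24%.** In part of those trials the overall test is also significant and the planned post-hoc comparison runs. The part that fits the concern is about 9% or 13%.
- **Toxicity will not be compared between doses.** The article describes no such comparison, but it says adverse events will be analysed, and safety tables by arm may sit in the full protocol or analysis plan, which is not shown. The abstract's toxicity question is also against afatinib alone, not dose against dose.
- **DCR has no room for improvement.** The Discussion's "median PFS: 9–12 months" concerns patients on EGFR-TKIs in general. Turning it into a 12-week DCR needs an assumed exponential curve and treats being progression-free as the same thing as disease control. I do not rely on it.

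**Conclusion.** The concern holds as a mismatch between claim and design. Section 2.1 promises a dosing conclusion, while sections 2.13 and 2.14 make the only inferential comparison of the two doses conditional on an overall difference. Under 70/80/90% or 82/95/95%, that condition fails in about 72 to 82% of trials. Without the condition, 85% versus 95% would be detected in about 9 to 18%, with an interval of about ±17 to ±21 points.

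These sizes depend on assumed DCRs and a 5% alpha. With 50/70/90% the condition fails in only 23 to 40% of trials, and a very large dose difference such as 50% versus 90% would have 68 to 85% power by the usual formula in an unconditional test. For moderate differences, the trial can inform the choice of dose but cannot settle it. With two equally effective doses, a one-sided pattern of significance with no dose comparison behind it arises in about 9 to 13% of trials at 82/95/95%. That is a risk of misreading, and the plan contains nothing that guards against it.

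**What to change.** 1. In Trial design, replace the statement that the results will provide the dosage with one saying that they will inform the choice of dose for a later trial.
2. Report, whatever the overall test shows, the DCR difference 1944 mg minus 972 mg, and each dose minus placebo, with 95% confidence intervals. Give the same estimates for the adverse-event proportions already collected under CTCAE. If the analysis plan already contains the safety estimates, a cross-reference is enough.
3. State that a difference in significance against placebo will not be read as a difference between the doses.

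The cost is some wording and a few extra tables from data already being collected. The dosing claim becomes weaker, and the intervals will be wide and will show openly how little this sample size can say about dose.

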**Table 2 T2:**
[figure not shown]
Summary of study design.

### Recruitment and consent

2.2

A total of 66 subjects with locally advanced or metastatic EGFR mutation-positive NSCLC who need afatinib therapy will be recruited at Kosin University Gospel Hospital, Busan National University hospital. All candidates will undergo a standardized interview and receive clinical study information about the trial. Written consent will be obtained from each participant. The purpose, procedures, and potential risks and benefits of the study will also be explained thoroughly to the participants. The participants will be able to withdraw from the study at any time without consequence. The trial covers the period from September 2018 to October 2020, including the enrolment and follow-up periods (Fig. 1).

**Figure 1 F1:**
[figure not shown]
Study flow chart.

### Inclusion criteria

2.3

Participants meeting the following criteria will be included:

1.19 years of age or older;2.Diagnosed with locally advanced or metastatic NSCLC, but unable to undergo surgery or radiation therapy;3.Histologically or cytologically EGFR-positive and requiring afatinib therapy;4.Presence of a lesion that can be measured by using chest X-ray, computed tomography (CT) or magnetic resonance imaging (MRI) with a single diameter or two diameters;5.Eastern Cooperative Oncology Group (ECOG) performance status score from 0 to 2;6.Life expectancy of more than six months, as well as normal bone marrow function and solid organ function for more than 6 months:(a)Bone marrow: ANC ≥ 1.5 × 10^9^/L, platelet ≥10 × 10^9^/L, and hemoglobin ≥10 g/dL,(b)Liver function: AST/ALT levels below twice the normal upper limit,(c)Kidney function: creatinine levels below twice the normal upper limit;7.Voluntarily signed written informed consent to participate in this trial.

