### Exclusion criteria

2.4

Participants meeting one or more of the following criteria will be excluded:

1.Experience with severe drug hypersensitivity to a particular drug or inability to take oral drugs;2.Currently pregnant or breastfeeding (fertile women will be required to use adequate contraception during the study period);3.Presence of metastatic cancer in the central nervous system or in need of concurrent therapy, such as primary site radiation therapy, chemotherapy, or immunotherapy;4.T790 M (threonine-to-methionine amino acid change at position 790) of the EGFR kinase domain (acquired, re-biopsy) mutation-positive;5.The presence of other serious disease:(a)Uncontrollable congestive heart failure or unstable angina, myocardial infarction within 1 year of study participation, uncontrollable hypertension or high-risk arrhythmia,(b)Inability to understand the research content due to neurological or psychiatric disorders, such as dementia and seizures,(c)Uncontrollable infections, such as tuberculosis and hepatitis;6.A history of diagnosis or treatment of malignant tumors other than NSCLC;7.Participation in research involving the combined administration of any other drug, except for afatinib, and in any other clinical trial within the previous 2 weeks;8.A need for administration of immuno-inhibitors or platinum-based chemotherapy after a PD-L1 expression test with multiple metastases with symptoms;9.Use of a prohibited medication during this clinical trial;10.Unsuitable for this clinical trial as determined by the researcher.

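### The platelet minimum in inclusion criterion 6(a) is printed as 10 × 10^9/L, far too low for the marrow requirement it defines and probably a misprint

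*Protocol article*

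**What the plan says.** Section 2.3 (Inclusion criteria), item 6, combines a life-expectancy requirement with a requirement for "normal bone marrow function and solid organ function for more than 6 months". Three sub-items then put numbers on it:

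- **Marrow, 6(a):** an absolute neutrophil count (ANC) of at least 1.5 × 10^9/L, "platelet ≥10 × 10^9^/L", and "hemoglobin ≥10 g/dL".
- **Liver, 6(b):** "AST/ALT levels below twice the normal upper limit".
- **Kidney, 6(c):** creatinine under the same twofold ceiling.

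The platelet limit appears only here. None of the ten items in section 2.4 (Exclusion criteria) mentions platelets or bleeding. The one that could apply is the general item 10: "Unsuitable for this clinical trial as determined by the researcher". Section 2.15 (Safety assessment) says that "complete blood analyses will be recorded at baseline prior to administration of the drug".

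**The concern.** The number contradicts the requirement it is meant to define. A patient with a platelet count of 10 to 20 × 10^9/L is profoundly thrombocytopenic, yet satisfies the platelet part of 6(a) as written. The other two values in 6(a) are ordinary limits for adequate marrow, so the platelet value alone is out of scale. The article gives no reason for admitting severely thrombocytopenic patients, so a deliberate choice is implausible.

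An eligibility limit decides who is exposed to trial treatment. If the printed value is also the one sites screen against, the numeric platelet check gives almost no protection, and participant safety rests on investigator judgement. The article is dated January 2020 and the stated trial period runs to October 2020, so the figure was published while the planned trial period was still open.

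**Working it through.** The platelet limit is a stated value with no formula behind it, so there is nothing to reproduce. The check is whether it is on the same scale as the limits around it.

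**Inputs from section 2.3:** ANC floor 1.5 × 10^9/L; platelet floor 10 × 10^9/L; haemoglobin floor 10 g/dL; liver and kidney ceilings at 2 times the upper limit of normal.

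**Assumed inputs (not in the article):** adult lower limits of normal (LLN) of 1.5 to 2.0 × 10^9/L for ANC, 130 to 150 × 10^9/L for platelets and 12 to 13 g/dL for haemoglobin; candidate intended platelet floors of 100 and 75 × 10^9/L.

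**Step 1, units.** 10 × 10^9 per litre ÷ 10^6 microlitres per litre = 10,000 per microlitre.

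**Step 2, each floor as a percentage of the LLN** (100 × floor ÷ LLN):

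| Limit | At the higher LLN | At the lower LLN |
|---|---|---|
| ANC 1.5 | 1.5/2.0 = 75.0% | 1.5/1.5 = 100.0% |
| Haemoglobin 10 | 10/13 = 76.9% | 10/12 = 83.3% |
| Platelets 10 (printed) | 10/150 = 6.7% | 10/130 = 7.7% |
| Platelets 75 (if intended) | 75/150 = 50.0% | 75/130 = 57.7% |
| Platelets 100 (if intended) | 100/150 = 66.7% | 100/130 = 76.9% |

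**Step 3, distance from normal.** The printed floor is 130/10 = 13 to 150/10 = 15 times below the LLN. Criterion 6 does use the word normal loosely, but its widest stated tolerance is twofold, for liver and kidney. For 10 × 10^9/L to lie within twofold of normal, the LLN would have to be 2 × 10 = 20 × 10^9/L. No plausible LLN is near that, so the conclusion does not depend on the exact range assumed.

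**Step 4, size of the likely slip.** If 100 was meant, the printed value is 100/10 = 10 times too low. If 75 was meant, it is 75/10 = 7.5 times too low. Of the two, 100 lies closer to the ANC and haemoglobin floors and needs only one lost zero.

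**Step 5, is it corrected or backed up elsewhere?** No other part of the article gives a platelet limit. Within the article, only the word normal in the criterion's opening and exclusion 10 could stop a patient who meets the printed figure.

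**The case against.** The strongest reply is that this is a journal article condensing a protocol that is not shown. Sites screen from the full protocol and from the e-CRF instructions supplied by the sponsor (section 2.16), so the figure may be a misprint in print only, with no participant affected. This stands as a limit on what can be concluded: the article shows that the published threshold is wrong, not that a wrong threshold was applied.

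Second, the sub-item sits under an opening that requires normal marrow function, and a patient with 10,000 platelets per microlitre would fail that on any sensible reading. The patient must also meet the ANC, haemoglobin and life-expectancy requirements, and exclusion 10 is a further stop. These safeguards are real but imperfect. The criterion itself relaxes the word normal for liver and kidney, and a numeric limit exists so that entry does not hang on interpretation.

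Third, no harm specific to this trial is shown. The afatinib toxicities named in the Discussion are diarrhoea, rash or acne, and stomatitis or mucositis, and the article states no platelet effect for HAD-B1. The number of patients who could enter on the printed figure cannot be derived. That is correct, and no such number is claimed.

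Fourth, the percentages rest on reference limits from outside the article. They do, but the gap is too wide for any reasonable choice to close.

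Finally, a digit lost when the PDF was read cannot be wholly excluded. The inequality sign, unit, exponent and neighbouring values are all intact, so nothing points to that.

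**Conclusion.** The concern holds. The printed platelet minimum of 10 × 10^9/L cannot define normal, or even adequate, marrow function: it is about 7% to 8% of an assumed lower limit of normal of 130 to 150 × 10^9/L. The text has to be corrected whichever document holds the right value.

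The cause is most probably typographical. That 100 × 10^9/L was intended, making the printed value ten times too low, is an assumption the article does not confirm. Whether the trial's screening was affected remains open until the full protocol is checked. The error concerns eligibility and safety and has no bearing on sample size, power or type I error.

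**What to change.** 1. Check the intended platelet minimum against the full protocol. The candidate is 100 × 10^9/L, for the clinical team to confirm.
2. Correct criterion 6(a), and any screening checklist or e-CRF edit check that repeats the printed figure.
3. If the full protocol already has the right value, publish a correction to the article; nothing more is needed.
4. If the full protocol has the same figure, amend it and review the baseline platelet counts of participants already enrolled, using the pre-dose blood results planned in section 2.15.

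The cost is one value in the criterion and in any document that copies it. The participant review arises only under step 4 and needs no new data collection.
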